### Interventions

The intervention consists of an IEMT protocol using the Orygen Dual Valve (Forumed S.L, Barcelona, Catalonia, Spain). This device allows patients to train inspiratory and expiratory muscles simultaneously, and loads can be adjusted independently at regular intervals of 10 cmH_2_O. Training load was set to the inspiratory and expiratory pressures allowing patients to perform 10 maximal repetitions (RM), and adjusted weekly by 10 cmH_2_O if tolerated. Patients performed five sets of 10 inspirations and expirations, three times a day, 7 days per week, for 8 weeks. The control group received the same training schedule using a sham valve. Patients of both groups received standard therapy consisting of swallowing manoeuvres, oral exercises and compensatory techniques aimed at improving self-management of dysphagia and protect the airway. The training session was supervised by a Speech and Language Therapist (SLT) twice a week, and the other sessions were self-assisted at home.

There are no special criteria for discontinuing or modifying allocated interventions. Patients requiring discontinuing or modifying the interventions were withdrawn from the study. Strategies to improve adherence to respiratory training included providing a record sheet to register the home training sessions. Concomitant SLP therapy or respiratory therapies (oxygen therapy, breathing treatments, humidity-aerosol therapy, pulmonary drainage procedures, respiratory exercises, exercises with a triflow device…) were not permitted during the trial.

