### Sample size

Accepting an alpha risk of 0.05 and a beta risk of 0.2 in a two-sided test, 25 patients are required in each group to detect a difference of 27 (SD 31) cmH_2_O in PImax, anticipating potential losses of 15% (final size 50 patients). These assumptions have been based on data of de Menezes et al. [14]. The sample size was calculated using the GRANMO Sample Size and Power Calculation software of the Hospital del Mar Research Institute (IMIM).

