### Allocation

This trial was designed as a parallel-group double-blind randomized controlled trial with allocation ratio 1:1 in a superiority framework of the intervention and intention-to-treat analyses. Allocation to study groups was performed independently by a member of the medical staff blinded to patient identity using a randomization programme designed by the IT Department. Patients and researchers in charge of assessments were blinded to study group assignments. Patients were randomly allocated to either an intervention (IEMT) group or a control (sham) group. Allocation concealment was ensured as the person in charge of randomization did not release the randomization codes until participants completed all measurements. Training began at hospital discharge. Outcome measures were collected by a trained research worker at baseline (week 0), at the end of training (week 8) and 6 months after cessation of training. Data collection and analysis are carried out by a research worker blinded for the allocation group.

Study sites and phases are summarized in the flow chart diagram (Fig. 2).

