### Statistical analysis

Descriptive statistics summarizes the demographic and clinical outcomes of the participants. Assumption of normality is analysed using normality charts and the Kolmogorov-Smirnov test corrected with the Lilliefors test. The bivariate analysis is performed using the chi-square, Fisher exact, Student t or Mann-Whitney U tests, depending on the variables analysed.

Treatment effect is analysed in two ways: changes in PImax and PEmax pre- and post-intervention (ΔPImax and ΔPEmax, respectively) and by calculating the percentage change using the formula [((post value − pre-value) /pre-value) × 100]. Changes during follow-up are assessed by analysis of variance using mixed repeated measures and a one-factor design for the analysis of values over time.

All statistical tests are two-tailed and statistical significance has been set at 0.05. IBM SPSS 22.0 software is used for statistical analysis. The final report will follow CONSORT 2010 guidelines.

When estimating the study’s sample size, the possibility of loss to follow-up was considered and factored into the calculation. Moreover, other missing data was accounted for by handling drop-outs as non-finishing intervention, in accordance with the intention-to-treat principle.

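### The protocol claims intention-to-treat, but patients who stop or modify training are withdrawn from the study and the missing-data rule gives them no outcome value

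*Protocol article*

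**What the plan says.** The last paragraph of the Introduction and the Allocation section both describe a 1:1 parallel-group trial "in a superiority framework of the intervention and intention-to-treat analyses".

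The Interventions section says there are no special criteria for discontinuing or modifying the allocated intervention, and then: "Patients requiring discontinuing or modifying the interventions were withdrawn from the study". The withdrawal is from the study, not only from training. The same section makes a weekly 10 cmH2O load adjustment, subject to tolerance, part of the planned intervention.

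The Statistical analysis section measures the treatment effect as the pre-to-post change in PImax and PEmax and as the percentage change from the pre value. For follow-up it states: "Changes during follow-up are assessed by analysis of variance using mixed repeated measures and a one-factor design for the analysis of values over time". On missing data it says that losses were allowed for in the sample size, and that the remainder was dealt with by "handling drop-outs as non-finishing intervention, in accordance with the intention-to-treat principle".

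Trial status reports that enrolment closed with 48 patients in March 2020 and that follow-up ended in September 2020.

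**The concern.** An intention-to-treat comparison keeps each randomised patient in the assigned arm whatever the adherence. The Interventions rule makes unmodified adherence a condition of staying in the study. The Statistical analysis section then presents an adherence label as if it satisfied intention-to-treat.

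Such a label could serve for a binary outcome, where not finishing might count as failure. For a continuous change score it does nothing: without a week-8 value there is no change to compute, and the patient leaves the comparison.

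At stake is whether the arms being compared are still the randomised arms. If the patients who leave differ in outcome from those who stay, and do so unequally between arms, the estimated effect on a primary outcome is shifted and the stated 5% error rate no longer holds. Enlarging the sample for losses protects power but does not address this.

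**Working it through.** **1. The plan's own figure.** Inputs from Sample size: difference 27 cmH2O, SD 31, two-sided alpha 0.05, beta 0.2, 15% losses.

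n per arm = 2 × [31 × (1.960 + 0.842) / 27]² = 20.69, rounded up to 21. Allowing for losses, 21 / 0.85 = 24.7, rounded up to 25 per arm, 50 in total. This matches the protocol; the sample size is not in question.

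**2. The statements side by side.**

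- Introduction and Allocation: all randomised patients are to be analysed as allocated.
- Interventions: those who need to stop or modify training leave the study.
- Outcome formulas: change = post − pre; percentage change = (post − pre) / pre × 100. Both need a post value.
- Statistical analysis: drop-outs receive a label. No outcome value or estimation method is attached.

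No section says that withdrawn patients were still measured at week 8 or at 6 months. If they were not, the change-score comparison contains completers only. This is an inference from the withdrawal rule and the formulas; the protocol does not state it.

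**3. Size of the possible bias.** From the document: SD 31, taken here as the SD of the change in PImax, and 48 enrolled, hence 24 per arm. Assumed, because the document gives neither: the fraction d withdrawn in each arm, and the correlation ρ between the tendency to withdraw and a poor change in PImax.

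If an arm loses a fraction d, the mean of those who remain shifts by ρ × SD × φ(z_d) / (1 − d), where z_d is the normal quantile at d and φ the normal density.

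For d = 0.15: z = −1.036, φ = 0.233, and 0.233 / 0.85 = 0.274. Then 31 × 0.274 = 8.5 cmH2O at ρ = 1. Multiplying by ρ gives 2.6 at ρ = 0.3, 4.3 at ρ = 0.5 and 0 at ρ = 0.

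Type I error of a completers-only t test, nominal 5%, from 40,000 simulated trials with no true effect:

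| Withdrawn, training / sham | ρ | Bias (cmH2O; + favours training) | Type I error |
|---|---|---|---|
| 15% / 0% | 0.3 | +2.5 | 5.7% |
| 15% / 0% | 0.5 | +4.3 | 7.4% |
| 15% / 0% | 0.8 | +6.8 | 11.0% |
| 25% / 5% | 0.5 | +4.9 | 8.0% |
| 5% / 25% | 0.5 | −4.9 | 7.9% |
| 15% / 15% | 0.3 to 0.8 | about 0 | about 5% |

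The simulated biases agree with the formula to within simulation error. Against the 27 cmH2O target, 2.6 is 10%, 4.3 is 16% and 8.5 is 31%.

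**The case against.** **It could be a reporting gap only.** The missing-data sentence can be read as keeping drop-outs in their assigned arm, merely classed as not having finished, and the article does not say that they went unmeasured. This stands in part: it is why completers-only is an inference. But that reading still gives no value for an unmeasured patient, so the claim to intention-to-treat remains unsupported.

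**The estimator belongs in an analysis plan.** Leaving out a model or an imputation method would indeed be no finding in an article. Here the article makes a positive statement and calls it intention-to-treat, and a withdrawal rule determines whether the outcome exists at all. That contradiction is in the text.

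**Stronger readings that the documents do not support:**

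- *The analysis is biased toward training.* A reader might infer this because only real loads become hard to tolerate. No withdrawals by arm or reason are given. Sham patients could also leave, for example for lack of benefit. The mirror pattern favours sham, and equal withdrawal by the same mechanism gives no bias.
- *Any change in load removes the patient.* Adjustment subject to tolerance is part of the plan, so not raising the load is not a withdrawal trigger. This also weakens the argument that escalation drives patients out.
- *The bias is about 9 cmH2O with 18% to 19% type I error.* That results from removing exactly the four smallest changes among 24 training patients and nobody from sham. It is an extreme, and the protocol's 15% loss allowance is not confined to one arm.
- *The follow-up analysis deletes everyone with a missed visit.* A conventional repeated-measures analysis of variance would, but the wording does not fix the procedure. The point does not depend on it.

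**Conclusion.** Wrong as written. The missing-data rule does not deliver the intention-to-treat analysis that the protocol declares, and the withdrawal rule works against it. That much rests on the text alone.

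The practical consequence, a completers-only comparison for the change scores, holds unless withdrawn patients were still measured.

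The bias is possible, and its sign is unknown. Bias toward training is plausible but not established. With 15% lost from training and none from sham, it runs from 0 to 8.5 cmH2O. The moderate part of that range is about 2.6 to 4.3 cmH2O, with type I error of about 5.7% to 7.4%. These figures rest on assumed withdrawal rates, an assumed correlation and the protocol's SD of 31.

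**What to change.** Reconcile the Introduction, Interventions, Allocation and Statistical analysis sections, and state whether withdrawn patients were measured at week 8 and 6 months. Then:

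- **Replace the non-finishing clause** with an analysis of all randomised patients in their assigned arm, using every value obtained, including any obtained after training stopped.
- **PImax and PEmax:** use a likelihood-based mixed model with baseline as one of the repeated outcomes, or multiple imputation. Patients with only a baseline value then stay in the analysis. With baseline as a covariate only, a patient lacking both later values has no outcome row and drops out again.
- **Sensitivity analysis:** neither method corrects for withdrawal that depends on the unobserved outcome. Add an analysis for data not missing at random, for example imputation of missing training-arm values from the sham arm.
- **Dysphagia severity:** this primary outcome is scored on an ordinal scale and needs a method suited to that.
- **Reporting:** give withdrawals by arm and reason.
- **Naming:** follow-up has ended, so values never taken cannot be recovered. If withdrawn patients were not measured, call the main analysis set completers or available-case, and do not claim intention-to-treat.

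The cost is a little more analysis and possibly a less favourable estimate; no further patients are needed. No view is taken on when training should be stopped or modified.

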### Data monitoring and harms

Given the non-pharmacological nature of this study, a data monitoring committee is not required. Any adverse effect related to the exercise intervention or any unintended effect was registered. There are no anticipated problems that could be detrimental to the participant. Interim analyses are not contemplated, but if required, only the main investigators will be involved.

### Steering committee and audits

No steering committee was constituted. The principal investigators supervised correct development of the trial. A monthly meeting was held to detect any eventual difficulties or errors. Both investigators were responsible for the design of the trial but did not participate in data recruitment or intervention. They met with the intervention group every 6 months, to detect and correct any eventual difficulties during the recruitment and follow-up processes, data management and monitoring and statistical analysis of outcomes. They were responsible for assessing the rate of progress to ensure that the trial was conducted in accordance with the study plan.

No intermediate audits were contemplated. But should any unexpected adverse effects appear, audit process will be carried out in order to detect and correct the side-effects.

## Ethics and dissemination

### Research ethics approval and consent

National and international research ethics guidelines were followed, including the Deontological Code of Ethics, Declaration of Helsinki and current confidentiality laws concerning personal data in Spain (Organic Law 3/2018, December 5th) and the European Union *(European Parliament and Council Regulation EU 2016/619)*. Detailed, understandable oral and written information was provided to patients and family members, and an informed consent to participate will be signed by all participants (Additional File 1 A and B). The Retornus-2 study protocol and the informed consent process were reviewed and approved by the Clinical Ethics Committee of the *Institut Hospital del Mar d´Investigacions Mèdiques*, Barcelona, Spain (*Comité Ètic d’Investigació Clínica Parc de Salut Mar*: reference number 2016/6796/I) (Additional file 2).

Prior to any intervention, each patient was informed about the risk and the goals of the current study. Patients were allowed to withdraw from the study at any time for any reason. Patients received the required treatment regardless of participation in the study.

### Protocol amendments

Participants, the research team and trial registries were notified of any eventual modifications of the study protocol.

*Confidentiality* included in data management

*Declaration of interest/Competing interests* (included in the Declarations section)

*Access to data/Availability of data and materials* (included in the Declarations section)

*Ancillary and post/trial care* (included in the Declarations section)

### Dissemination policy

The findings of this research project will be disseminated nationally and internationally in scientific meetings, and we will seek publication in peer-reviewed journals.

## Discussion

This study is an attempt to evaluate the effect of IEMT on respiratory muscle function and dysphagia severity. Adherence to the 8-week protocol was ensured by using an external device for training. Retornus-2 is the natural follow-up of the first study of our group, the Retornus I study, in which we reported that inspiratory and expiratory muscle training (IEMT) induces significant improvement in inspiratory and expiratory muscle strength and could potentially offer an additional therapeutic tool aimed at reducing respiratory complications at 6 months in stroke patients [5]. Secondly, adding IEMT to Standard Swallowing Therapy (SST) was effective and feasible and provided a safe approach to improving respiratory muscle strength and swallow function [16]. This second study is the result of the difficulties encountered in implementing the training protocol in acute patients (Retornus-1). The main difference between trials was to train the patient during admission in rehabilitation (acute post-stroke phase, Retornus-1) or at discharge when the patient returned home (> 1 month post-stroke event, Retornus-2). The authors consider that this trial will contribute evidence for the development of new strategies for accelerating recovery from dysphagia and the use of external devices.

In conclusion, the results of the trial may result in important advances in neurological dysphagia rehabilitation. First, the magnitude of effect on dysphagia may be higher than previous trials, where the focus is placed on improving respiratory strength. Second, the trial tests the capacity of patients for training at home, facilitating rehabilitation intervention. Finally, if the results lead to a reduction in hospital admissions, respiratory muscle training could help reduce direct and indirect costs associated with stroke.

### Strengths and limitations of the study

Samples from rehabilitation units usually have an initial bias because patients tend to be preselected for their potential to follow a rehabilitation programme. This is an initial bias due to the fact that not all the stroke patients are admitted to follow an intensive rehabilitation programme and some of them are transferred to other facilities (e.g. nursing home). Patients in our study were recruited during their stay in the neurorehabilitation ward (intensive rehabilitation). Once functional status was enough to return home, our Health System provided transport facilities to continue the rehabilitation programme.

The decision to only evaluate patients in a subacute stroke phase may provide limited results and make extrapolation to other populations difficult. The homogeneity of participants due to selected-dysphagic post-stroke events impacts on the applicability of our findings to the general stroke population but not for a population similar to the sample described in this study.

## Trial status

*Protocol version number:* Retornus-2_2

*Begin recruitment:* 05/07/2017

*End recruitment:* 03/31/2020

*End data collection:* 09/31/2020

*Trial status:* Enrolment is completed

*Statement about trial status:* Because of the COVID-19 pandemic, enrolment was closed in March 2020 with 48 patients (in sample size calculation, an overhead of 15% was calculated). The follow-up ended in September 2020.

## Data Availability

The datasets generated and/or analysed during the current study are not publicly available due to the amount of data generated but are available from the corresponding author on reasonable request.

## Abbreviations

RMT: Respiratory muscle training
IEMT: Inspiratory and expiratory muscle training
EMT: Expiratory muscle training
VFSS: Videofluoroscopy swallowing study
RCT: Randomized control trial
MIP: Maximum inspiratory pressure
MEP: Maximum expiratory pressure
SSP: Swallowing and speech pathologist
